### Interim analyses {21b}

Not applicable. No interim analysis is planned due to the use of validated and standardized procedures.

### Methods for additional analyses (e.g., subgroup analyses) {20b}

Not applicable. No subgroup analysis is planned.

### Methods in analysis to handle protocol non-adherence and any statistical methods to handle missing data {20c}

Statistical analysis will be conducted with participants who adhere to the intervention, while non-adherent participants will be excluded from the analysis. Adherence to the intervention will be monitored at each session. Participants will be considered “adherent” to the intervention if they attend at least 15 sessions (75%). A drop-out rate of 25% was considered in the power calculation; therefore, per-protocol analysis will be conducted.

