### Trial design {8}

FEARFALL is a randomized controlled prospective trial with a duration of 3 years. Older adults will be randomly allocated into parallel groups of equal sizes (1:1). The study will be conducted double blind. Participants will be randomized into either intervention (IG) or sham control group (SCG), with the study designed to determine the superiority of the effectiveness of the IG compared to the SCG. While each employee of the project can perform recruitment and baseline assessment, the intervention will be carried out exclusively at the Institute for Biomedicine of Aging by trained exercise instructors. The Chair of Health Psychology will be responsible for the outcome assessment, allowing for blinding with regard to group allocation of the participants. All biological specimens will be analyzed by staff at Chair of Health Psychology in the laboratories physically separated from all other project locations. The study complies with the Declaration of Helsinki and Guidelines for Good Clinical Practice. The flow diagram for FEARFALL is shown in Fig. 1.

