### Criteria for discontinuing or modifying allocated interventions {11b}

Criteria for discontinuing the intervention for a participant is an adverse event such as a fall or accident resulting in severe injuries (e.g., fractures), which permanently prevents their participation in the intervention.

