### Outcomes {12}

As the primary outcome, the decrease in CaF after intervention (T1) measured by FES-I score in comparison to the SCG will be confirmed. All secondary outcome measures will be assessed at three time points (T0, T1, and T2) and changes between groups over time will be explored. Therefore, sarcopenia will be assessed by BIA, physical function will be tested by SPPB, and handgrip strength and physical activity will be tested by actigraphy. The VAS scale of EQ-5D will determine health-related quality of life. General psychological status will be explored with questionnaires for depression (GDS), perceived stress (PSS), and anxiety (GAS). Furthermore, MMSE and TMT A and B will determine cognitive function.

Pathophysiological parameters changes will be explored in blood samples such as levels of CRP, IL-6, TNF-alpha, and IL-10 for systemic inflammatory processes as well as gene expression of IL-1beta, IL-6, IL-10, and I-kappa B for intracellular inflammatory activity. In addition, stress system activity will be measured by changes in cortisol and alpha-amylase levels in salivary samples.

If a fall or accident resulting in severe injuries (e.g., fractures) occurs during the intervention period, it poses a potential risk to the participants and is therefore considered an adverse outcome.

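### The only analysis this article describes for a superiority trial is per-protocol, so the FES-I comparison at T1 is open to selection bias of unknown direction and size

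*Protocol article*

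**What the plan says.** Trial design {8} describes a 1:1 randomised trial, "with the study designed to determine the superiority of the effectiveness of the IG compared to the SCG". Outcomes {12} makes the T1 FES-I comparison primary: "the decrease in CaF after intervention (T1) measured by FES-I score in comparison to the SCG will be confirmed".

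The analysis population is set in {20c}: "Statistical analysis will be conducted with participants who adhere to the intervention, while non-adherent participants will be excluded from the analysis". Participants count as adherent "if they attend at least 15 sessions (75" per cent). The section ends with its reason: "A drop-out rate of 25% was considered in the power calculation; therefore, per-protocol analysis will be conducted".

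The article names no intention-to-treat or full analysis set, no sensitivity analysis and no method for missing data. Section {20a} gives no other population for FES-I, and {20b} reads "Not applicable. No subgroup analysis is planned". The preregistration cited in {7} and {20a} is not shown, so the statement here is limited to this article.

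**The concern.** A superiority claim rests on randomisation, which makes the arms comparable at the start. Under {16c}, allocation follows consent and baseline assessment, so attendance is known only afterwards and may depend on what the arm offers. The intervention group does progressive strength, balance and CaF training. The sham group has lectures, light stretching and upper-limb exercise. Section {11c} also describes special retention efforts for the sham group. Staying for 15 sessions may therefore select different kinds of people in the two arms.

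The reason given in {20c} does not support the choice. Enlarging a sample for drop-out protects precision when data are absent. It does not justify removing people who attended too few sessions but can still be measured. The section treats these two groups as one.

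Section {11b} supplies an example: "Criteria for discontinuing the intervention for a participant is an adverse event such as a fall or accident resulting in severe injuries", on condition that the injury permanently prevents taking part. If this happens before session 15, the participant leaves the FES-I analysis, although such a fall could plausibly raise concerns about falling.

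The primary comparison is at stake, and so are the other between-group comparisons, because {20c} is not limited to one outcome.

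**Working it through.** **1. Adherence threshold.** Under Intervention, weeks 1-4 have two supervised sessions a week and weeks 5-16 have one: 4 × 2 + 12 × 1 = 20. Then 0.75 × 20 = 15, which matches {20c}. The sham sessions have the same frequency, so the rule can be applied in both arms, although {20c} does not say outright that it is.

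**2. The plan's sample size.** Sample size {14} gives f = 0.15, alpha 0.05, power 0.95, correlation 0.50, ε = 1 and n = 154. It states neither the number of measurements nor the form of the test. Assume two groups, two measurements (T0, T1) and the repeated-measures within-between F test:

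- λ = f² × N × m / (1 − ρ) = 0.0225 × 154 × 2 / 0.5 = 13.86, with df 1 and 152. Power is 0.959, consistent with the stated 0.95.
- With ρ = 0.5 the SD of change equals the SD of a single score. Setting λ = N × δ² / 4 = 0.09 × N gives δ = 0.60 SD of change as the implied planning effect.

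**3. How many could be excluded.** At the 25-30% loss in {14}, 50-60 of 200 leave and 150-140 remain. Power is then 0.954-0.941 if f = 0.15 holds among those kept. Precision is therefore not the difficulty.

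**4. What selection can do.** Assumptions, not from the documents: no true effect, 100 per arm, 70% kept in each arm, and adherence driven by a normal latent variable with correlation r to FES-I improvement.

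- The mean shift among those kept is r × φ(z) / 0.70, with z = Φ⁻¹(0.30) = −0.524 and φ(z) = 0.348. The factor is 0.348 / 0.70 = 0.497.
- With r = 0.3 in one arm and 0 in the other, bias = 0.3 × 0.497 = 0.149 SD of change.
- The standard error is about √(2/70) = 0.169, and 0.149 / 0.169 = 0.88.
- Type I error = 1 − Φ(1.96 − 0.88) + Φ(−1.96 − 0.88) ≈ 0.14.

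Simulation of the same model agrees (IG = intervention group, SCG = sham control group; a negative bias favours the IG):

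| r in IG / SCG | Kept in IG / SCG | Bias (SD of change) | Type I error |
|---|---|---|---|
| 0.3 / 0.3 | 70% / 70% | about 0 | about 5% |
| 0.2 / 0.1 | 70% / 70% | −0.05 | about 6% |
| 0.3 / 0.3 | 70% / 80% | −0.04 | about 6% |
| 0.3 / 0 | 70% / 70% | −0.15 | about 14% |
| 0 / 0.3 | 70% / 70% | +0.15 | about 14% |

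**5. Power with all 200 analysed.** If f = 0.15 holds for everyone, λ = 0.09 × 200 = 18 and power is 0.988. If the 0.60 SD holds only in adherers and 25-30% gain nothing, the effect is 0.60 × 0.75 = 0.45 to 0.60 × 0.70 = 0.42 SD. Power is then 0.89-0.84, and 0.95 would need about 258-296 analysed.

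**The case against.** The strongest reply is that nothing in the article shows the bias to be large or to favour the intervention. Session frequency is equal in the two arms, participants are told that two methods are being compared, and reminders go to everyone. If non-improvers leave both arms alike, the comparison of those who stay is close to unbiased. This stands. A reader might infer that the bias favours the intervention group because people whose concerns do not improve stop coming. The same reasoning applies to the sham group, and selection there alone reverses the sign. The documents do not support a directional claim.

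Nor should the injury example be read as automatic exclusion. It needs a permanent bar to taking part that arises before session 15, it can occur in either arm, and no frequency is given.

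Some planned analyses are not randomised comparisons. Objective 1 concerns associations, and Objective 4 concerns success within the intervention group. The point is confined to comparisons between arms.

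The power cost is real. Recruitment was due to finish in May 2024, so the sample may not be expandable. That is a reason to state the cost, not to keep an analysis whose bias cannot be bounded from the plan.

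It might also be said that the population is a matter for an unseen analysis plan. Here the article makes an explicit choice and gives a reason for it, so it can be judged as written.

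**Conclusion.** The point holds. Section {20c} fixes a per-protocol population as the only one described in this article for a superiority trial, and the reason it gives does not follow. The T1 FES-I comparison and the other between-group comparisons are open to selection bias.

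Its size is unknown. Under the assumptions above it ranges from nothing, with type I error near 5%, to about 0.15 SD of change in either direction, with type I error near 14%. The larger figure is a quarter of the 0.60 SD planning effect (0.15 / 0.60), and that effect itself assumes two measurements and the within-between F test.

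A reader might go further and conclude that an FES-I difference could not be credited to the intervention at all. The documents do not support that. They show that the protection of randomisation is given up, not that the result must be wrong.

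**What to change.** Rewrite the whole of {20c}, including its last sentence. Changing only the first sentence would leave the per-protocol commitment in force. The new text should say that:

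- the primary FES-I analysis includes all randomised participants as allocated, whatever their attendance;
- T1 and T2 assessments are sought from non-adherent participants and from those who discontinued the intervention;
- missing data are handled by a named method, for example a likelihood-based mixed model or multiple imputation;
- the 15-session per-protocol analysis is kept as a labelled sensitivity analysis, with a statement that the rule applies in both arms.

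Cost: a change of wording and some extra follow-up contact. Section {18b} provides reminder calls and invitations in general but does not commit to following people who stopped attending, so that commitment has to be added. The estimated effect may be diluted. Sample size {14} should therefore restate power for the all-randomised analysis: about 0.89-0.84 with 200 analysed if 25-30% are non-adherent and gain nothing, under the assumptions given above.

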### Objectives {7}

The main and overarching objective of the project is to understand the role of the psychobiological stress response, including stress system alterations and inflammation, in the vicious cycle between CaF, declines in mobility, and development of muscle loss and sarcopenia. Therefore, a well-established intervention aimed at reducing CaF and increasing activity will be performed, to test whether a reduction of CaF can break the vicious cycle, and stop the downward spiral towards sarcopenia.

The specific objectives of the study are described in the following:*Objective 1*: To test whether CaF in older adults are positively related with altered stress system activity, specifically overactivity of the sympathetic nervous system (SNS) and hypoactivity of the hypothalamus–pituitary–adrenal (HPA) axis, and higher levels of systemic low-grade inflammation. It will additionally be tested whether general psychological symptoms (stress, anxiety, depression) are similarly or more strongly associated with stress system activity.*Objective 2*: To test whether a well-established CaF-reduction and exercise program reduce CaF will differentially affect stress system activity and reduce or slow down systemic low-grade inflammation. It will additionally be tested if and how general psychological symptoms (stress, anxiety, depression) are affected by the intervention.*Objective 3*: To test for directionality of the brain-to-immune/immune-to-brain feedback system by investigating whether reduced CaF precede reductions in inflammation (or lower rate of increase) or whether reductions in inflammation precede reductions in CaF (or lower rate of increase) (or both). It will additionally be tested whether general psychological symptoms (stress, anxiety, depression) provide an alternative or additional pathway.*Objective 4*: To test whether higher inflammation at baseline is predictive of lower success in the intervention group.*Objective 5*: To test whether systemic and intracellular inflammation at T0 is associated with lower decreases of CaF from T0 to T1 and T0 to T2.

This project has been preregistered before the start of data evaluation; see osf.io/m84hq.

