### Intervention

The intervention group will take part in a 16-week multicomponent exercise intervention.

During the initial 4 weeks, training sessions will take place twice a week, with supervised 60-min sessions at the IBA, where the participants will be familiarized with the components of the program. From week 5 to week 16, one supervised session per week will be provided at the IBA, and two 30-min sessions will be completed by participants as an unsupervised home program. An adherence rate of 75% in the intervention sessions will be considered as successful participation [54–57].

The multicomponent intervention will contain elements of gait, balance, and strength exercise to improve physical function and elements of the “Matter of Balance” program to reduce CaF [58]. The time points and frequency of the different exercise and behavioral components in the intervention are summarized in Table 2 and described in detail in the following.

**Table 2 Tab2:** Time points and frequency of the intervention components

	**Month**				**Total**
**Intervention components**	1	2	3	4	
Strength training	2	2	1	1	6
Challenging balance training	2	2	2	2	8
Functional training		1			1
Gait training	1		1		2
Body awareness		1		1	2
CaF training		1	2	1	4
Home program	1			1	2

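### Objective 4 asks who succeeds in the intervention group, but the 15-session rule first removes everyone below the protocol's own cut for successful participation, which can bias the answer or leave nothing to estimate

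*Protocol article*

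**What the plan says.** Four statements in the protocol article bear on this point.

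- **Objectives {7}, Objective 4:** "To test whether higher inflammation at baseline is predictive of lower success in the intervention group". Success is not defined there.
- **Objectives {7}, Objective 5:** a separate aim, whether "systemic and intracellular inflammation at T0 is associated with lower decreases of CaF from T0 to T1 and T0 to T2".
- **Intervention:** "An adherence rate of 75% in the intervention sessions will be considered as successful participation". This is the only participant-level criterion in the article that uses the language of success.
- **Methods in analysis to handle protocol non-adherence {20c}:** participants count as adherent "if they attend at least 15 sessions (75" per cent), and "non-adherent participants will be excluded from the analysis". The section ends: "therefore, per-protocol analysis will be conducted". No objective is exempted.

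**The concern.** An objective about who succeeds needs people who did less well in the data. The analysis-set rule removes participants by attendance, which is observed only after baseline. For Objective 4, attendance may be the outcome itself or may lie on the path from baseline inflammation to benefit. A null result could then mean that inflammation does not limit success, or only that the people in whom it did so had already been excluded. The analysed set would not tell these apart.

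This is a stated rule, not a detail left to an analysis plan. An analysis plan that followed it would inherit the problem. So would an arm-by-inflammation interaction fitted in the same adherent set.

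**Working it through.** **1. Are the two 75% cuts the same?** The Intervention section gives the schedule: "During the initial 4 weeks, training sessions will take place twice a week", then "From week 5 to week 16, one supervised session per week will be provided at the IBA".

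- Supervised sessions: 4 × 2 + 12 × 1 = 20, and 0.75 × 20 = 15. The stated figure is reproduced.
- With the two weekly home sessions added, the total is 20 + 12 × 2 = 44, and 15/44 = 34%. The 15-session rule therefore refers to supervised sessions.

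The cut for successful participation and the cut for entering the analysis coincide.

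**2. Success read as participation.** Everyone analysed has met the criterion. The outcome has variance 0 and no association is estimable.

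**3. Success read as an outcome, such as FES-I reduction.** The documents give no figure for inflammation against attendance or attendance against benefit, so every coefficient below is an assumption.

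Let X be baseline inflammation and A attendance, both standardised, with corr(X, A) = −r. Let success be Y = bA − cX + noise, and keep the top 75% on A. The 25% removed borrows the protocol's drop-out figure; the actual non-adherent share is not given.

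- Variance of A after the cut: z = −0.674, λ = φ(z)/0.75 = 0.424, V = 1 + zλ − λ² = 0.535.
- Full-group slope of Y on X: −(c + br).
- Adherent-set slope: −(c + brk), with k = V / [1 − r²(1 − V)].
- For r = 0.2, 0.3 and 0.4, k = 0.545, 0.558 and 0.578.

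Share of the full-group slope that remains, (c + brk)/(c + br), for r = 0.2 to 0.4 and b = 0.3 to 0.5:

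| Direct effect c | Share remaining |
|---|---|
| 0 (inflammation acts only through attendance) | 54–58% |
| 0.1 | 72–83% |
| 0.2 | 79–89% |

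**4. Other structures, also with the lowest 25% removed.**

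| Assumed structure | Full slope | Adherent slope |
|---|---|---|
| Attendance unrelated to inflammation | −0.40 | −0.40 |
| Inflammation lowers attendance, attendance does not affect success | −0.40 | −0.40 |
| Inflammation lowers attendance; an unmeasured factor raises attendance and lowers success | −0.40 | −0.46 |
| Inflammation raises attendance, attendance helps | −0.24 | −0.31 |

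The slope reached zero in none of the structures tried.

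**5. Precision in a middle case** (r = 0.3, b = 0.5, c = 0.1, variance of Y set to 1). The correlation is −0.25 in full and −0.19 in the adherent set. Two-sided power at 0.05 is Φ(atanh|ρ| × √(n − 3) − 1.96):

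- n = 100, ρ = 0.25: 0.2554 × √97 − 1.96 = 0.56, power 0.71.
- n = 75, ρ = 0.25: 0.2554 × √72 − 1.96 = 0.21, power 0.58.
- n = 75, ρ = 0.193: 0.1953 × √72 − 1.96 = −0.30, power 0.38.

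Of the total fall of 0.33, the loss of 25 people accounts for 0.13 and attenuation for 0.20. The first figure assumes a T1 FES-I in all 100 intervention participants. The Sample size section expects 25–30% drop-out, so 0.71 against 0.38 is an upper bound on what the rule costs.

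**The case against.** **The word success may mean effect.** The Intervention section speaks of successful participation and is never linked to Objective 4. The Sample size section uses the word for reduction of CaF, including in the intervention group. This stands, so the participation reading cannot be taken as established. It cannot be dismissed either: Objective 5 already covers the decrease in CaF, and Objective 4 would partly repeat it. The overlap is not decisive, because Objective 5 is not limited to the intervention group and names intracellular markers and T2.

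**The protocol's mechanism is biological.** The Background describes inflammatory cytokines blunting the anabolic effect of training. It does not say that inflamed people attend less. For response among those who trained, an adherent set is a defensible if imperfect choice. This also stands. It supports keeping that analysis, but not making it the only one.

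**A reader might infer that the association is necessarily pulled to zero or cannot exist.** The documents do not support that. It cannot be estimated on the participation reading only. On an outcome reading adherent participants still vary, and the direction and size of any bias depend on relations that the protocol does not report.

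**It follows from the general per-protocol rule, and the preregistration may define success.** An all-randomised analysis of every objective would resolve this point too. The preregistration is not shown and may settle the definition. Neither removes the difficulty here: the article states the exclusion without exception, and Objective 4 is harmed in a specific way because the selection variable may be its own outcome.

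**Conclusion.** The point holds in a limited form. The session arithmetic is exact: the analysis-set rule and the criterion for successful participation are the same cut, 15 of 20 supervised sessions. If success in Objective 4 means participation, it is constant in the analysed set and the objective cannot be answered.

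If it means an outcome, the restriction can bias the association. The most plausible direction is towards zero, provided that inflamed participants attend less and attendance drives benefit. Illustratively, 54% to 89% of the full-group slope remains. That range rests wholly on assumed coefficients and an assumed 25% removed; no bias and a strengthened association are both possible. The power figures are upper bounds on the loss. The change is worth making because the plan's answer otherwise depends on an untested assumption that conditioning on attendance is harmless.

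**What to change.** State what success means in Objective 4 and exempt that objective from the 15-session rule. Analyse all intervention-group participants with T0 inflammation data, on two outcomes:

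- (a) FES-I at T1 adjusted for T0, in everyone with a T1 value, whatever their attendance;
- (b) the number of supervised sessions attended (0–20), which needs no T1 visit.

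Keep the adherent-only result as a sensitivity analysis. If the objective is recast as a two-arm interaction, use the same unrestricted approach in both arms.

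The cost is a few sentences of analysis wording. Attendance is already monitored at each session, and inflammation is already measured at T0. There are two small downsides: (a) includes people who received little of the programme, and its gain in power is limited to non-adherent participants who still attend T1, a number the protocol does not give.
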